## Abstract

**Background:**

Drug-drug interactions (DDIs) are a major concern, especially for older adults taking multiple medications. Although Health Canada and the US Food and Drug Administration (FDA) use population-based studies to identify adverse drug events, detecting harmful DDIs is challenging due to the millions of potential drug combinations. Traditional pharmacoepidemiologic studies are slow and inefficient, often missing important harmful DDIs.

**Objective:**

This protocol outlines a novel approach to efficiently identify harmful DDIs using administrative health care data.

**Methods:**

Using high-throughput computing, we will conduct multiple population-based, new-user cohort studies using Ontario’s linked administrative health care data. The cohorts will be selected from the population of Ontario residents aged 66 years and older who filled at least one oral outpatient drug prescription from 2002 to 2023. In each cohort, the exposed group will comprise individuals who are regular users of one drug (drug A) who start a new prescription for a second drug (drug B); the referent group will comprise regular users of drug A not taking drug B. We will evaluate 74 acute outcomes within 30 days of cohort entry, including hospitalizations, emergency department visits, and mortality. Propensity score methods will balance exposed and referent groups on more than 400 baseline health characteristics. Modified Poisson and binomial regression models will estimate risk ratios (RRs) and risk differences (RDs). To ensure findings are both statistically and clinically meaningful, we will apply prespecified thresholds for effect sizes (eg, lower bounds of 95% CIs≥1.33 for RRs and ≥0.1% for RDs) and control the false discovery rate at 5% using the Benjamini-Hochberg procedure to address multiplicity. Subgroup and sensitivity analyses, including negative control outcomes and E-values, will assess robustness.

**Results:**

In a preliminary analysis, we identified approximately 3.8 million older adults who filled prescriptions for over 500 unique medications during the study period (2002-2023), and therefore, approximately 200,000 potential drug combinations will be available for study. The initial drug pair cohorts had a median of 583 new users per cohort (IQR 237-2130); the median overlap in drug pair prescriptions was 57 days (IQR 30-90). The protocol was finalized on August 30, 2025, and outlines the analysis of data from 2002 to 2023. The analysis is scheduled to be completed by fall 2026, with results interpreted in 2027. The final manuscript submission is planned for December 2028.

**Conclusions:**

This study aims to identify credible signals of harmful DDIs in older adults in routine care. This study will use an innovative approach that leverages data from provincial administrative health care databases and integrates high-throughput computing and rigorous pharmacoepidemiologic methods to generate robust real-world evidence that can inform safer prescribing practices and regulatory decision-making.

**International Registered Report Identifier (IRRID):**

DERR1-10.2196/77224

## Introduction

Drug-drug interactions (DDIs) occur when two or more medications interact in ways that alter their effectiveness or safety [1,2]. The drug being affected is termed the *object drug*, while the drug causing the interaction is known as the *precipitant drug* [3,4]. The precipitant drug can influence the object drug through pharmacokinetic (PK) mechanisms (affecting absorption, distribution, metabolism, or excretion) or pharmacodynamic (PD) mechanisms (altering the drug’s effects at its target site) [3]. An interaction may increase the effect of an object drug, leading to toxicity. Alternatively, an interaction may lessen the effect of an object drug, leading to reduced efficacy or treatment failure [5].

DDIs pose a significant risk for older adults due to polypharmacy and age-related changes in drug metabolism and elimination [6-8]. Approximately one in six hospitalizations among older adults is attributed to adverse drug events [9]. Additionally, older adults are often excluded from clinical trials, limiting our understanding of how DDIs affect this population. Drugs with a narrow therapeutic index are particularly concerning, as even minor interactions can have serious clinical consequences [10,11].

Although premarket clinical trials evaluate PK DDIs in healthy volunteers, many clinically significant DDIs are only identified after drug approval through case reports, small observational studies, and large-scale pharmacoepidemiologic research [12,13]. Traditional DDI detection methods often analyze one drug pair at a time, which can be slow and inefficient. These limitations are a concern worldwide: international efforts using electronic health records, claims data, or national prescription registries have made progress, but such approaches may not scale fast enough to keep pace with the thousands of new drug combinations entering the market each year, highlighting the need for rapid, large-scale, and systematic surveillance methods.

High-throughput computing and automated analytical pipelines have been applied in other contexts to rapidly screen for potential DDIs. For example, researchers in the United States and Europe have used these approaches with large electronic health care databases to identify clinically relevant DDI signals [14,15]. Bykov et al [14] validated a case-crossover–based method by successfully flagging known interactions in large US claims databases. Similarly, Leonard et al [15] demonstrated the ability of high-throughput pharmacoepidemiologic screening using a self-controlled case series design to confirm known DDI risks and identify novel potential interactions in real-world data. Although Bykov et al [14] and Leonard et al [15] have demonstrated the potential of high-throughput screening for DDIs in US health care databases using self-controlled designs, our study complements and extends these approaches by applying high-throughput computing to Ontario’s population-based, linked administrative health care data within a universal health care system using a population-based, new-user cohort design [16]. This will allow us to systematically evaluate over 200,000 medication combinations in older adults, integrating PK, PD, and epidemiologic evidence for robust, real-world signal detection at a scale and scope not previously achieved. By applying these methods in a Canadian context, we aim to identify potentially harmful DDIs that may warrant further validation, address key knowledge gaps, and generate findings relevant to both national and international health care systems. To the best of our knowledge, this represents the first application of such an approach in Canada, leveraging the strengths of a universal health care setting to further enhance the generalizability and clinical relevance of detected DDI signals. The results of this work have the potential to support safer prescribing practices, generate signals that could inform clinical decision-making once validated, and guide health care policy aimed at reducing adverse drug events in older adults.

This protocol outlines our plan to detect harmful DDIs more efficiently in routine care using high-throughput computing and automation. To do this, we will simultaneously conduct more than 200,000 population-based, new-user drug safety studies using 21 years of data from Ontario’s administrative health care databases (2002-2023). These databases contain encrypted data on all health care visits and hospitalizations of Ontario residents—all of whom have universal access to hospital care and physician services through a government-funded single-payer system, with Ontarians aged 65 years and older also receiving universal outpatient prescription drug coverage.

Following the application of inclusion and exclusion criteria, we will analyze a refined set of medication cohorts, each containing an exposed group (individuals prescribed a certain pair of medications) and a referent group (individuals prescribed a single medication). The exposed and referent groups will be statistically balanced on more than 400 baseline health characteristics. We will assess 74 clinically relevant outcomes and conduct extensive sensitivity and bias analyses to minimize false discoveries. Harmful DDIs that meet prespecified criteria will be further examined in additional and exploratory analyses. This study’s objective is to identify credible signals of harmful DDIs in older adults in routine care.

## Methods

### Study Design and Data Sources

Using high-throughput computing and automation, we will conduct over 200,000 population-based, new-user drug safety cohort studies using linked administrative health care databases in Ontario, Canada. The study period will span from July 1, 2002, to March 1, 2023. All study data will be obtained from Ontario’s linked administrative health care databases housed at the Institute for Clinical Evaluative Sciences (ICES) [17]. These databases contain encrypted, person-level data for Ontario residents, who have universal access to hospital care and physician services through a government-funded, single-payer system. A description of the databases is provided in Table 1.

**Table 1 table1:** Description of study databases.

Database		Description
**National databases/registries**		
	Canadian Institute for Health Information’s Discharge Abstract Database (CIHI-DAD)	Contains diagnostic and procedural information for all hospitalizations, collected by each province
	Canadian Organ Replacement Register (CORR)	National registry that includes information on vital organ transplantation and dialysis activities
	National Ambulatory Care Reporting System (NACRS)	Contains information on hospital and community-based ambulatory care visits
**Ontario databases**		
	Ontario Mental Health Reporting System (OMHRS)	Contains adult inpatient mental health information
	Registered Persons Database (RPDB)	Contains information on patient demographics, including sex, birth dates, and death dates
	ICES^a^ Physician Database (IPDB)	Contains physician-related information, such as birth dates, sex, education, and specializations
	Ontario Drug Database	Contains claims for prescription drugs received under the ODB^b^ program
	Ontario Health Insurance Plan (OHIP)	Contains diagnostic information and health claims for inpatient and outpatient services
	Ontario Laboratories Information System (OLIS)	Contains laboratory test orders and results from hospitals, community labs, and public health labs

^a^ICES: Institute for Clinical Evaluative Sciences.

^b^ODB: Ontario Drug Benefit.

Residents aged 65 years and older receive universal outpatient prescription drug coverage through the Ontario Drug Benefit (ODB) program (while residents of all ages only receive universal prescription drug coverage for medications dispensed in emergency departments or during hospital admissions). Consequently, our study will leverage comprehensive outpatient prescription data for residents aged 65 years and older. We have previously used these databases to examine adverse drug events and health outcomes [16,18-21].

These databases are expected to be complete for all study variables, except for prescriber specialty (10%-20% missing), rural residence, and neighborhood income quintile (less than 2% missing). The only source of loss to follow-up is emigration from Ontario, which occurs at an estimated rate of 0.5% per year [22].

The study conduct and reporting will adhere to recommended guidelines for observational pharmacoepidemiology studies that use routinely collected health data (Multimedia Appendix 1) [23,24]. More details on the databases, study variables, and the codes used to define baseline comorbidities are provided in Multimedia Appendix 2. The integration of data from different sources is summarized in Multimedia Appendix 3. The process of building the cohorts is summarized in Figure 1, and the analytic steps are summarized in Multimedia Appendix 4.

**Figure 1 figure1:**
[figure not shown]
Study flow diagram. DAD: Discharge Abstract Database; NACRS: National Ambulatory Care Reporting System; ODB: Ontario Drug Benefit; OHIP: Ontario Health Insurance Plan; RPDB: Registered Persons Database.

### Source Population

The source population will comprise adults aged 66 years and older who filled at least one oral outpatient drug prescription with a supply duration of at least 3 days, dispensed between July 1, 2002, and March 1, 2023 (codes for nonoral versions are provided in Multimedia Appendix 5). The age criterion will ensure that individuals in this population have at least 1 year of prior ODB prescription drug coverage.

### Cohort Builds

The study cohorts will be constructed using the process described later. Each cohort will be selected from the source population and contain an exposed group (individuals prescribed a pair of medications: drugs A and B) and a referent group (individuals prescribed drug A), as defined next.

#### Regular Users of Drug A

We will first select individuals with at least two prescriptions for the same medication (drug A) within a 210-day period, with a maximum allowable gap equivalent to 150% of the days’ supply of the previous prescription.

#### New Users of Drug B

From the sample of regular users of drug A, we will select individuals who start a prescription for a new medication (drug B) that is taken concurrently with drug A, meaning drug B’s start date is on the same date as the most recent drug A fill date or falls within drug A’s supply duration.

#### Cohort Entry Dates for Exposed and Referent Groups

The exposed group will comprise regular users of drug A and new users of drug B, as described earlier. The cohort entry date for individuals in the exposed group will be the start date of drug B. The referent group will comprise regular users of drug A who are not coprescribed drug B. The cohort entry date for individuals in the referent group will be assigned based on the distribution of the time differences between the most recent prescription for drug A and the initiation of drug B for individuals in the exposed group, ensuring similar observation periods between groups [25].

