#### Individual-Level Exclusion Criteria Applied to the Exposed and Referent Groups

We will exclude individuals who meet any of the following criteria:

Individuals prescribed drug B within 180 days before the cohort entry date (to ensure those in the exposed group are new users of drug B and that those in the referent group were not previously exposed).Individuals prescribed another medication in the same class as drugs A and B on the cohort entry date. For example, if drug A or B is sertraline, which is a serotonin reuptake inhibitor (SSRI), individuals prescribed a nonsertraline SSRI on the cohort entry date will be excluded.Individuals discharged from the hospital or emergency department within 2 days before the cohort entry date (to ensure that prescriptions are new outpatient prescriptions).Individuals whose day supplies for drug A or B are ≥100 days or <2 days.Individuals who are nonpermanent Ontario residents, are aged <66 or >105 years on the cohort entry date, or have a date of death on or before the cohort entry date (data cleaning exclusions).

An individual can only enter a cohort once; if an individual meets the eligibility criteria multiple times, the first eligibility date will serve as the cohort entry date.

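### Drug A supply at cohort entry is required of the exposed group only; the rule that dates referents does not keep them within their own supply

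*Protocol article*

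**What the plan says.** All references are to the Methods of the protocol article.

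- **Regular Users of Drug A** asks for at least two fills within 210 days, "with a maximum allowable gap equivalent to 150% of the days’ supply of the previous prescription".
- **New Users of Drug B** ties exposed entry to coverage, with "drug B’s start date is on the same date as the most recent drug A fill date or falls within drug A’s supply duration" as the condition.
- **Cohort Entry Dates for Exposed and Referent Groups** sets exposed entry: "The cohort entry date for individuals in the exposed group will be the start date of drug B". For the comparison group it says: "The referent group will comprise regular users of drug A who are not coprescribed drug B". Referent dates are "assigned based on the distribution of the time differences between the most recent prescription for drug A and the initiation of drug B" in the exposed group. The stated aim is similar observation periods, and a methods reference is cited.
- **Individual-Level Exclusion Criteria**, which apply to both groups, remove "Individuals whose day supplies for drug A or B are ≥100 days or <2 days", so supplies of 2 to 99 days remain. The other exclusions concern prior drug B, same-class drugs, recent discharge and data cleaning. None concerns drug A supply on the entry date.

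**The concern.** The contrast is meant to be drug A plus drug B against drug A. Every exposed patient holds drug A supply at time zero by construction. For a referent, the stated rule needs only a drug A fill and a gap borrowed from the exposed group. If that gap exceeds the referent's own days' supply, and the referent has not refilled, follow-up starts with no drug A in hand.

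To the extent this happens, the comparison becomes A plus B against a mixture of A and no A. Where drug A itself raises the risk of the outcome, the pair looks more harmful than it is. Where drug A protects, a true signal can be masked. The same rule builds every one of the roughly 200,000 drug-pair cohorts, and the Benjamini-Hochberg correction addresses multiplicity, not bias.

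**Working it through.** The article gives no figure for this point, so there is none to reproduce. Two things can be checked: whether any stated rule closes the gap, and how large the effect could be under stated assumptions.

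**Does another rule close it?**

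- The regular-user rule tolerates a gap of 150% of the previous supply. For a 30-day fill the next fill may come at day 45 (gap counted from the fill date) or day 75 (counted from the end of supply). That does not ensure coverage on a later assigned date.
- The exclusions do not mention drug A coverage at entry.
- The propensity covariates named in the article include prior use of drug A and dispensing within 120 days. A referent dated to day 60 after a 30-day fill still counts as dispensed within 120 days.
- The 1:1 matched analysis is described without any further coverage condition. The negative-control analysis uses a period starting 90 days before entry, so it does not test coverage at entry.

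**Share of referents off supply.** The assumptions, none from the article, are:

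- drug A fills last 30 or 90 days, with share p on 90 days, the same in both groups;
- drug B starts on the fill day in share m, and otherwise evenly over the exposed patient's own supply;
- gaps are assigned regardless of the referent's supply;
- a share r of referents whose gap exceeds their supply has refilled and is still covered.

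Only a gap from a 90-day fill given to a 30-day referent can overshoot, and it does so for 60 of the 90 days:

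f = p(1 − p) × (60/90) × (1 − m) × (1 − r)

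A simulation agreed with this formula.

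**Effect on the risk ratio.** If drug A alone has risk ratio RR_A against no drug A, and f is the off-supply share of referents, the pair's ratio is multiplied by

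RR_A / [(1 − f) × RR_A + f]

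This treats drug A's effect as wholly absent in off-supply referents and wholly present in everyone else for 30 days.

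| p | m | r | f | Multiplier, RR_A = 2 |
|---|---|---|---|---|
| 0.5 | 0 | 0 | 16.7% | 2/1.833 = 1.09 |
| 0.5 | 0 | 0.5 | 8.3% | 2/1.917 = 1.04 |
| 0.5 | 0.3 | 0.5 | 5.8% | 2/1.942 = 1.03 |
| 0.5 | 0.5 | 0.8 | 1.7% | 2/1.983 = 1.01 |
| 0.1 | 0 | 0 | 6.0% | 2/1.940 = 1.03 |
| 0.1 | 0.5 | 0.8 | 0.6% | 2/1.994 = 1.003 |
| 0 or 1 | any | any | 0% | 1.00 |

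At f = 16.7% the multiplier is 3/2.667 = 1.125 for RR_A = 3, and 0.5/0.583 = 0.86 for a protective drug A with RR_A = 0.5.

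The 16.7% is the maximum for a 30/90 mix, because p(1 − p) peaks at 0.5. It is not a bound for every mix. An assumed 7/30/60/90-day mix (10/40/10/40%) gives 5.4% to 10.7% with half refilled and m from 0.5 down to 0; with no refills it gives 11.0% to 21.6%.

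**Against the signal threshold.** The lower confidence limit for the risk ratio must reach 1.33. At the 9% end, an undistorted lower limit of 1.33/1.09 = 1.22 would be enough to reach it.

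**The case against.** The strongest reply is that silence in a condensed article is not a flaw. The article says only that dates are based on the gap distribution and cites a method. That method, the study flow figure or the appendices may confine dates to the supply window, and the Introduction and Discussion clearly intend referents to be on a single drug. This stands as a limit on certainty: the code may already be right. It does not dispose of the point, because the article spells out the on-supply condition for one group, gives a different rule for the other, and lists exclusions for both without it.

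A reader might go further and infer three things that the document does not support.

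- **That off-supply referents have stopped drug A.** Being past supply is not stopping. On the 50/50 inputs with no refills, 0.25 × 45/90 = 12.5% of referents would be past day 45 and only 0.25 × 15/90 = 4.2% past day 75, the two readings of the article's own tolerated gap.
- **That 17% is the expected share.** It needs an even 30/90 mix, no refills and no same-day starts, although the article expressly allows same-day starts.
- **That weighting cannot repair it.** The article names only examples from more than 400 covariates. If days' supply and time since fill are in the model, off-supply referents would have very low propensity scores, and the trimming and odds weights would remove or shrink them. The named covariates do not show this, and the full list is not at hand.

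It is also fair that the distortion is modest next to a lower limit of 1.33, which is joined by a risk-difference threshold, false discovery control and sensitivity analyses.

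**Conclusion.** The point holds as a badly fixed eligibility rule. Coverage by drug A at time zero is required of the exposed and not of the referents, and the stated dating rule can place a referent past the end of supply whenever days' supply varies between patients.

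The asymmetry is plain in the text; its size is unknown. Under assumed 30/90-day mixes (p from 0.1 to 0.9, m up to 0.5, r up to 0.8) the off-supply share runs from about 0.6% to 17%. With RR_A = 2 this inflates the pair's ratio by under 1% to about 9%. The effect is nil if supplies are equal, gaps are matched on supply, or every affected referent has refilled. The shares are unweighted, so the propensity weights could lower them. The bias is modest in any one cohort but has a predictable direction for a given drug A and outcome, and so merits correction before the analysis is run.

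**What to change.** In Cohort Entry Dates for Exposed and Referent Groups, apply to referents the condition already set for the exposed: the assigned date must fall on the fill date, or within the days' supply, of that referent's most recent drug A fill. Draw the gap within strata of drug A days' supply, or as a fraction of supply elapsed, and redraw where it overshoots. Carry the same condition into the 1:1 matched analysis, and report the on-supply share at entry by group for each cohort that yields a signal.

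The cost is one condition in the cohort-building code and one sentence in the protocol. A few referents will be lost or re-dated. If the code already does this, the sentence alone is enough.
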